**Data collection procedure**

The data collection procedure will be the same as outlined in the pilot study. Flow chart for data collection is illustrated in the Consolidated Standards of Reporting Trials (CONSORT) in Appendix L.

***Participant recruitment***

The co-researchers who are nurses in the oncology units will introduce the mPEI programme to eligible women. For those interested, their eligibility will be confirmed by the co-researchers. They will be given detailed information about the study after which their consent will be sought to join the study. For those that consent, they will be required to complete and sign a consent form.

***Blinding***

The RAs will be blinded alongside the healthcare team. The patients will be aware of the intervention they are receiving, likewise the intervener (the researcher) will also be aware of the intervention; hence, they will not be blinded.

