***Technical Support***

The research assistants will train the intervention group for 30minutes on how to install and use the app. Participants will be given the telephone number of the developer so they can call in case of any technical issue that needs to be fixed during the application usage. They can also drop a text message, or a voice note for the developer. Technical assistance will be provided 8:00am to 5:00pm from Monday to Friday.

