***Design***

An assessor-blinded, two-arm RCT using a parallel group will be adopted. Qualitative data will also be collected from an online focus group discussion to assess the acceptability, perceived usefulness, and ease of usage of the intervention.

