***Research assistant training***

Two research assistants (RAs) that were previously trained in qualitative data collection will be further trained for one hour on subject recruitment and quantitative data collection using the data collection instruments. Their ability to properly administer the instruments will be tested through interrater reliability.

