***Data collection***

The data collection will be conducted by two research assistants. Quantitative data will be conducted at baseline and immediately after the completion of the programme while qualitative data will be collected immediately after the programme completion. Data collection will be done at the oncology clinic. An information sheet which contains details of the intervention will be administered (Appendix I) after which the consent form will be completed (Appendix J).

The recruitment capability will be measured by documenting the recruitment rate, consent rate, and refusal rate based on the number of patients who are screened, those who are eligible, those who finally agree to be part of the study, and those who sign the informed consent form. Their reason for ineligibility and refusal to be part of the study will also be documented.

The acceptability and feasibility of the intervention will be assessed by documenting the attrition rate and the reason for lost to contact, adherence rate based on the number of participants that fully adhere to the protocol and data collection procedure, reasons for not adhering and any other adverse occurrence will be noted.

The acceptability of the intervention wi also be measured by a qualitative data collection. Three sessions of online, synchronous (live) focus group discussions with five participants in each group will be conducted by the research assistants. Online focus group discussion was considered appropriate for this part of the study due to its cost-effectiveness, no time commitment required for the participants to travel to the facility, ease of moderation and compatibility with the overall study design which is an online-delivered intervention (Rezabek, 2000). Questions for focus group interview in this phase is found in Appendix K. The focus group interview will explore the participants’ comments on acceptability of the intervention, ease of usage of the intervention and perceived usefulness of the intervention. Their findings will be used to improve the main intervention.

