**Fidelity of the intervention**

Fidelity of intervention refers to the degree of adherence to intervention protocol (Stein et al., 2007). To ensure fidelity in this study, the PI will obtain a certificate after participating in a training for health workers on psychoeducation for BC patients. The PI will also deliver all the sessions of the intervention. monitor and reinforce adherence to the program alongside provision of psychological support. This will ascertain consistency in the mode of delivery. The co-researchers that are experienced nurses working in the oncology units of the hospitals will provide nurse-consultancy services. The attendance rate of and response rate to the intervention will be monitored by the RAs. A personal link will be shared individually with the eligible participants to access the application. This link will be revoked after they are added. To prevent contamination, they will be instructed not to share the intervention content with any other patient. Process evaluation will be done to assess the fidelity of the intervention.

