During interaction on the mobile app, the participants will be free to use a name they are comfortable with or remain anonymous so their identity can be confidential. They will also be informed not to share the details of their interaction with anybody who is not part of the intervention to maintain privacy. Furthermore, they will not be required to display their personal pictures. Sensitive issues will not be raised during the interaction on the application. The application will not made available on social networking sites or public domains. Each participant will be given a unique link to download the application. After download, the link will be revoked. Each participant will create a unique username and password which they will be instructed not to share with any other person. They will be able to change the password anytime they desire. Data from the app will be encrypted and will only be accessible to the principal investigator and software engineer. The participants will be informed that the principal investigator and software engineer can access their profile. The principal investigator and the software engineer will be responsible for safekeeping of the data from the application during the study. Other study data will be safely kept by the principal investigator. The software engineer will transfer the data from the application to the principal investigator and supervisor after the study. The principal investigator will be responsible for keeping all study data in a locked cabinet after the study. All paper copies of the data will be destroyed by a paper shredder and all electronic copies will be permanently deleted from the computer and storage devices by the principal investigator five years after the study is completed and published. Principles of beneficence, non-maleficence, and trust will be upheld throughout the study.

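### The research assistants who collect the outcomes are declared blinded, but other tasks the protocol gives them reveal allocation before the post-intervention assessment

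*Protocol*

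**What the plan says.** All references are to the Protocol.

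- **Blinding (main RCT):** "The RAs will be blinded alongside the healthcare team". The same section says that the patients and the intervener are not blinded.
- **Design (pilot):** "An assessor-blinded, two-arm RCT using a parallel group will be adopted". The main RCT is called multicentre and does not carry the assessor-blinded label, so its blinding claim rests on the Blinding section alone.
- **Data collection (pilot):** "The data collection will be conducted by two research assistants", at baseline and directly after the programme, at the oncology clinic. The main RCT's Data collection procedure adopts the pilot procedure unchanged.
- **Research assistant training:** the section provides for a single pair: "Two research assistants (RAs) that were previously trained in qualitative data collection will be further trained for one hour on subject recruitment and quantitative data". No other RAs are described anywhere.
- **Technical Support:** "The research assistants will train the intervention group for 30minutes on how to install and use the app".
- **Fidelity of the intervention (main RCT):** "The attendance rate of and response rate to the intervention will be monitored by the RAs". This section also assigns the nurse consultations to co-researchers who are nurses in the hospitals' oncology units.

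**The concern.** Blinding the person who collects an outcome works only if that person's other duties do not disclose allocation. Here the duties themselves disclose it, so the problem is not a risk of accidental unblinding.

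The stake is bias at the point of collection. The primary outcome is a self-efficacy scale, and the secondary outcomes are also questionnaires. At the post-intervention visit, an intervention participant may give her answers to the person who taught her the app, while a control participant has had no such contact. Any prompting, or any wish to please, could then differ between arms in the direction of the hypothesis. The trial would also be reported with a safeguard that its own procedures remove. An analysis plan cannot repair this, because it depends on who does what at the sites.

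**Working it through.** The protocol gives no figure on this point, so the check sets its statements side by side.

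1. **Who collects the outcomes?** Two RAs (Data collection, pilot), carried into the main RCT by its Data collection procedure.

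2. **Are they the same people who train and monitor?** Technical Support refers to the research assistants without giving a number. Research assistant training describes two RAs, and no section mentions a further or unblinded team. That they are the same people is an inference, but it is the only one the text supports.

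3. **Does app training reveal allocation, and when?** Only the intervention group is trained, so the trainer must know who is in it. The training covers installing and using the app, so it comes before app use and therefore before the post-intervention assessment. Technical Support belongs to the programme design, so this applies to both the pilot and the main RCT.

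4. **Does monitoring reveal allocation, and when?** Controls receive standard care only and have no programme attendance to record. A participant with an attendance record is therefore an intervention participant. The sessions run over the six weeks before the post-intervention assessment. This task is written for the main RCT.

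5. **Does the conclusion need both tasks?** No. Step 3 or step 4 alone contradicts the Blinding statement.

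6. **The other half of the sentence.** The healthcare team is also called blinded. Nurse-led consultation and Psychological Support give intervention participants calls of 15 to 20 minutes from oncology nurses in weeks one, three and five. Fidelity of the intervention places those nurses in the hospitals' oncology units. At least these members of the team know the allocation of the women they call.

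7. **The focus groups.** "Three sessions of online, synchronous (live) focus group discussions with five participants in each group will be conducted by the research assistants". That is 3 × 5 = 15 women, which equals the pilot intervention arm of 15. Focus groups and questionnaires are both placed directly after the programme, with no order given. If the questionnaires come first, the groups do not unblind those assessments. This item is therefore secondary, and the conclusion does not use it.

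**The case against.** The strongest reply is that assessor blinding matters little here. Every outcome is a patient-reported scale, and the patients are openly unblinded. Eligibility requires women who can read and write English and are able to complete the questionnaires, which suggests self-completion. Much of this stands: keeping the RAs blinded would remove only part of the reporting bias. But the mode of administration is not settled. Research assistant training tests how well the RAs administer the instruments through interrater reliability, which suggests an active role. A limited safeguard must still be described truthfully.

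A second reply is that monitoring could run on aggregate or pseudonymous records supplied by the PI. That is possible, but the protocol does not say so, and it would leave the app training untouched.

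Four stronger readings are tempting, and the documents do not support them:

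- A reader might infer that the RAs are the only blinded party. The Blinding section also names the healthcare team.
- A reader might see a direct contradiction with Ethical considerations: "Data from the app will be encrypted and will only be accessible to the principal investigator and software engineer". That sentence restricts app data. It does not prevent the PI, who runs every session, from passing on attendance records.
- A reader might treat the focus groups as equal proof. They are written for the pilot, reach the main RCT only through the general carry-over, and have no stated order relative to the questionnaires.
- A reader might attach an inflated false-positive rate. Any such figure needs an assumed shift in scores, and nothing in the protocol ties a shift of any size to the RAs rather than to the patients' own knowledge of their arm.

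**Conclusion.** The point holds as an internal contradiction. Followed as written, the protocol unblinds its outcome collectors before the post-intervention assessment, in the pilot through app training and in the main RCT through both training and monitoring. The statement that the RAs are blinded is therefore wrong, as is the pilot's assessor-blinded label. The healthcare-team statement is wrong at least for the nurses who give the consultations.

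This rests on one inference: that the RAs in Technical Support and Fidelity of the intervention are the two who collect the outcomes. If the sponsor intends different people, the protocol must say so.

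The size of the bias cannot be derived from the documents. What is lost is protection against bias introduced at data collection, because participant unblinding would remain in any case. The matter should be settled before enrolment, since an RA who has trained a participant cannot be blinded to her allocation again.

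**What to change.** 1. Restrict the RAs to collecting the baseline and post-intervention outcomes.
2. Move app training and the monitoring of attendance and response to the PI, who is already unblinded, delivers the sessions and has access to the app data. The developer can support installation. The nurses should not be assumed to be available for this: the protocol gives them no access to app data, and the Blinding section does not list them as unblinded.
3. If RAs run any focus groups, hold them only after all post-intervention questionnaires have been collected.
4. Correct the healthcare-team statement under Blinding so that it agrees with the nurse consultations.
5. If the tasks are not moved, delete the statement that the RAs are blinded and the assessor-blinded label in the pilot Design section, and report the trial as open-label.

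The cost is a short protocol amendment and some extra work for the PI. No new staff are needed.

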***Randomisation***

To reduce the chance for confounding, selection and accidental bias, while ascertaining that allocation of participants to the intervention and control groups is balanced (Efird, 2011); a block randomisation with a block size of four, six and eight using an allocation ratio of 1:1 will be conducted by an independent researcher who is not part of the research team. The participants will be randomised into two arms, intervention group who will receive the intervention and the control who will receive the standard care. Sealed sequentially numbered opaque envelopes will be assigned to each participant by the researcher.

**Process Evaluation**

As process evaluation is important in understanding and interpreting outcomes in trials (Khan et al., 2020), process evaluation will be conducted in this study to precisely determine how the intervention works and if this be the case, to further investigate how this intervention can be successfully implemented in standard clinical practice. The process evaluation will be guided by the Medical Research Council guidance for process evaluation of complex interventions (Moore et al., 2015). The three components emphasised in the framework as essential to understanding intervention outcomes will be explored which include: implementation, mechanisms of impact and context (Moore et al., 2015).

The objectives for the evaluation are to: (i) assess the dose and reach of the intervention, ii) assess the adaptability of the intervention features for individual needs of the participants, (iii) explore the mPEI program from the perspective of the participants and the nurses to gain a deeper insight into mechanisms underlying changes in outcomes while probing unexpected consequences, (iv) evaluate external factors that might have affected intervention delivery, and (v) investigate resources and implementation processes required for effective clinical implementation of the intervention. The convergence model by Creswell and Plano Clark, (2011) will be utilised during the process evaluation for analysis of quantitative and qualitative data.

**Data analysis**

SPSS version 25 will be used to analyse quantitative data. The demographic data and clinical data will be analysed through descriptive statistics including frequencies, percentages, mean and standard deviation. Continuous variables at baseline, and immediately after the intervention will be compared through independent samples t- test for the continuous variables and chi-square or Fisher’s exact test for the categorical variables where appropriate. Primary and secondary outcomes data will be analysed through the generalized estimating equation (GEE) model provided the assumptions for homogeneity of variance and normality are met (Bell et al., 2014). In a bid to control for attrition bias, the intention-to-treat principle will be used to account for loss to follow up (Nam & Toneatto, 2016).

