**Hypothesis**

It is hypothesised that participants who receive the mPEI, when compared with the control group at baseline and immediately after the intervention, will demonstrate significantly higher level of self-efficacy, coping, quality of life, and significantly lower level of symptom distress, anxiety and depression.

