***Sample size planning***

Sample size is calculated based on the primary outcome of self-efficacy. Power analysis was done with G*Power version 3.1 (Faul et al., 2007), and a medium effect size of 0.53 which was demonstrated in a previous mHealth psychoeducational study featuring women undergoing BC chemotherapy. Power was 0.8 and *p*<.05 with 10% attrition which was an average attrition rate found from a recent mhealth systematic review conducted on this population (Cohen 1988; Zhu et al., 2018). Sample size is estimated to be 126 participants, but the exact number will be confirmed after the pilot study.

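### The hypothesis places the treatment difference at baseline as well as after the intervention, and post-intervention self-efficacy gets both a t-test and a GEE with no single deciding contrast named

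*Protocol*

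**What the plan says.** The Hypothesis section predicts that intervention participants, "when compared with the control group at baseline and immediately after the intervention, will demonstrate significantly higher level of self-efficacy", with matching predictions for the secondary outcomes.

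The Data analysis section of the main RCT plans two things. First, "Continuous variables at baseline, and immediately after the intervention will be compared through independent samples" t-tests, with chi-square or Fisher's exact tests for categorical variables. Second, "Primary and secondary outcomes data will be analysed through the generalized estimating equation (GEE) model", on condition that homogeneity of variance and normality hold. It does not say which GEE coefficient tests the hypothesis, how the t-test and the GEE rank, or what replaces the GEE if the condition fails.

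The Sample size planning section of the main RCT states: "Sample size is calculated based on the primary outcome of self-efficacy". It uses "a medium effect size of 0.53 which was demonstrated in a previous mHealth psychoeducational study", then "Power was 0.8 and *p*<.05 with 10% attrition", and concludes: "Sample size is estimated to be 126 participants, but the exact number will be confirmed after the pilot study".

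**The concern.** Allocation is random and 1:1, so before treatment the arms differ only by chance. A hypothesis of superiority at baseline cannot be a hypothesis about the intervention, and a significance test at baseline says nothing about it. The wording also leaves the target open: it could be the post-intervention difference or the difference in change.

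The analysis section does not settle this. The t-test sentence covers continuous variables at both visits. Demographics are recorded on a separate sheet, and the scales that the protocol schedules at both visits are the outcome instruments, CBI-B included. Post-intervention CBI-B is thus compared once by t-test and again within the GEE. If the two disagree, the document does not say which one decides. Because the GEE is conditional on distributional checks, the choice could also be made after the data are seen. The candidate contrasts differ in power, so the choice has consequences.

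**Working it through.** **Inputs from the protocol.** Standardised effect d = 0.53, power 0.80, significance level 0.05, 10% attrition, N = 126 (Sample size planning, main RCT); 1:1 allocation (Randomisation); two assessments, before and immediately after the programme (Outcome measures).

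**Assumptions.** Two-sided test, since sidedness is not stated; equal SD at both visits, set to 1; complete data in those retained; baseline-post correlation r = 0.3, 0.5 or 0.7, since the protocol gives no value.

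**Step 1: reproduce the planned N.** A two-sided two-sample t-test with d = 0.53 and 80% power needs 56.86, so 57 per arm and 114 in total.
- Inflation as 114 × 1.1 = 125.4, rounded up, gives 126.
- Inflation as 114 / 0.9 = 126.7, rounded up, gives 127.
- The normal approximation gives 56 per arm, and 112 / 0.9 = 124.4, rounded up, gives 125.

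The stated 126 is therefore reproduced by an unadjusted two-group comparison of means. A one-sided test would need only 45 per arm (90 / 0.9 = 100) and does not fit. After 10% loss, 126 × 0.9 = 113.4 remain, or about 57 per arm.

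**Step 2: power of each contrast at 57 per arm.** The effect is 0.53 throughout and only the residual SD changes. The noncentrality is (0.53 / SD) × √(57/2).
- Post-intervention t-test: SD = 1.
- GEE group-by-time contrast (difference in change): SD = √(2(1 − r)).
- Baseline-adjusted difference (ANCOVA): SD = √(1 − r²).

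| r | t-test SD | power | group-by-time SD | power | adjusted SD | power |
|---|---|---|---|---|---|---|
| 0.3 | 1 | 80% | 1.183 | 66% | 0.954 | 84% |
| 0.5 | 1 | 80% | 1.000 | 80% | 0.866 | 90% |
| 0.7 | 1 | 80% | 0.775 | 95% | 0.714 | 98% |

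**Step 3: does the ordering depend on r?** The adjusted variance 1 − r² never exceeds 1, the t-test variance. It never exceeds the change variance either, because 2(1 − r) − (1 − r²) = (1 − r)² ≥ 0. Apart from one degree of freedom, the adjusted contrast is at least as powerful as either alternative at any r. The group-by-time contrast falls below the t-test when r is under 0.5.

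**Step 4: simulation check** (57 per arm, 400 runs per r; at r = 0.3, 0.5, 0.7).
- GEE group-by-time: 0.69, 0.82, 0.98.
- GEE with a common baseline mean: 0.86, 0.90, 0.99.
- ANCOVA: 0.86, 0.89, 0.99.
- t-test: 0.82, 0.78, 0.82.

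Where Step 2 has a matching figure, the two agree within about 3 percentage points. The GEE with a common baseline mean performs like ANCOVA.

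**The case against.** The strongest reply is that the hypothesis is loosely worded and nothing more. The Outcome measures section uses nearly the same phrase just to name the two assessment times, and the Study design section says that randomisation equalises the groups, so the authors hardly expect a baseline difference. The only sentence in the analysis section that names the primary and secondary outcomes assigns them to the GEE, and GEE terms are commonly left to the SAP, which is not at hand.

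Much of this is fair, and it limits the point. Three stronger readings are not supported:
- A reader might infer that baseline CBI-B goes unused. The protocol neither includes nor excludes it as a covariate. A two-visit GEE uses baseline scores as outcome data, and it could be fitted with a common baseline mean.
- A reader might infer that the trial is underpowered. It is not: the t-test that matches the stated N reaches the stated 80%.
- A reader might take the hypothesis to mean a group effect averaged over both visits, which would dilute the effect. The protocol specifies no such average.

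What the reply does not remove is the formal hypothesis as written, the outcome t-tests at both visits, and the lack of any ranking between t-test and GEE. Those come from what the protocol states, not from its silence on model terms.

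**Conclusion.** The point holds as a fault of wording and of an unsettled primary analysis. The hypothesis should not include a baseline difference, the baseline significance tests are uninformative after randomisation, and two unranked tests address the same post-intervention CBI-B comparison.

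There is no shortfall against the planned 80%. Reading the result from a group-by-time contrast instead of the t-test would cost about 14 points of power at r = 0.3 (80% to 66%), change nothing at r = 0.5 and gain about 15 points at r = 0.7. A baseline-adjusted contrast would add about 4, 10 or 18 points over the t-test. The sizes rest on the assumed correlation, equal SDs and 57 analysed per arm. That adjustment is at least as powerful as the other two contrasts does not depend on the correlation. Baseline adjustment is thus a free improvement, not the repair of a power deficit.

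**What to change.** 1. Restate the hypothesis: mean CBI-B immediately after the intervention is higher in the intervention arm than in the control arm. Reword the secondary predictions the same way.
2. Name one primary analysis: the between-arm difference in post-intervention CBI-B adjusted for baseline CBI-B. Fit it either by ANCOVA or by the planned GEE with a common baseline mean. Say which, and say that this single contrast decides the primary outcome.
3. Use the same form for the secondary outcomes.
4. Delete the baseline significance tests and the post-intervention t-tests on outcomes. Describe baseline scores by arm with summary statistics.
5. State in advance what is done if the assumption checks on the primary model fail, so that the deciding test is not chosen from the data.

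The cost is protocol wording. CBI-B is already collected at both visits, and the planned 126 participants need not change.

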***Outcome measures***

Data will be collected from the intervention and control group at baseline, and immediately after the completion of the intervention. All the instruments will be administered in English language which is the medium of instruction for the intervention.

*Self-efficacy for coping with cancer*

Self-efficacy for coping with cancer will be measured with the Cancer Behavior Inventory-Brief Version (CBI-B). The instrument comprises 12-items measuring confidence of individuals in performing activities that show how well they are coping with the demands of cancer and their treatment. Each item will be scored on a nine-point Likert scale with ‘1’ meaning ‘not at all confident’ and ‘9’ meaning ‘totally confident’. Higher scores indicate greater self-efficacy in coping. This instrument has been used in BC studies. It has also been validated and found reliable with a Cronbach’s α coefficient ranging from .84 to .88. (Heitzmann, 2001). (See Appendix C).

*Coping*

Coping will be assessed with Coping Orientation to Problems Experienced Inventory (Brief COPE). The scale can measure primary coping styles under three subscales: problem-focused coping, emotion-focused coping and avoidant coping. This 28-item instrument was developed as a short version of the original 60-item COPE scale (Carver et al., 1997). The 28 items are measured on a four-point scale (ranging from1= I haven’t been doing this at all, 2= a little bit, 3= a medium amount, and 4= I’ve been doing this a lot). The instrument has also been verified among patients with breast cancer receiving chemotherapy and have a fairly good reliability and validity. Internal consistencies ranged from 0.25 to 1.00, and intraclass correlation coefficient ranged between 0.05 and 1.00 (Yusoff et al., 2010). (See Appendix D).

*Anxiety and Depression*

Anxiety and depression will be assessed with the Hospital Anxiety and Depression Scale (HADS). The instrument has been used to measure anxiety and depression in BC patients. HADS comprises anxiety and depression subscales with seven items per subscale. A total score of 0-7 is normal, 8-10 is borderline abnormal and 11-21 is abnormal. This instrument has been validated and also found to be reliable with a Cronbach’s α coefficient of 0.79 for the anxiety subscale, 0.87 for the depression subscale, and 0.85 for all the items in an investigation into the psychometric properties in a previous study among BC patients (Rodgers et al., 2005) (See Appendix E).

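### The protocol allows its GEE analysis only if outcomes are normal with equal variances, which GEE with robust standard errors does not need, and it names no alternative if they are not

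*Protocol*

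**What the plan says.** The Data analysis section of the main RCT gives the analysis of the primary and secondary outcomes in one sentence. They will be analysed by GEE "provided the assumptions for homogeneity of variance and normality are met". The section gives no method for judging the two assumptions, no threshold and no replacement method. It does not say whether raw scores, change scores or residuals are to be examined.

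The only other between-arm method for continuous variables comes one sentence earlier: values at baseline and after the intervention "will be compared through independent samples t- test for the continuous variables". It is not presented as a fallback for GEE.

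The primary outcome is self-efficacy, as Sample size planning confirms: "Sample size is calculated based on the primary outcome of self-efficacy". Under Outcome measures it is scored with the 12-item CBI-B: "Each item will be scored on a nine-point Likert scale". There are two time points: "Data will be collected from the intervention and control group at baseline, and immediately after the completion of the intervention".

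**The concern.** GEE models the mean of the outcome. With sandwich standard errors, its large-sample inference rests on a correct mean model, independent participants and enough of them. It does not rest on a normal outcome or on equal variances in the two arms. The protocol therefore states a condition that the method does not have. By its title, the reference cited for the sentence is a review of how missing data are handled in trials, so nothing visible in the protocol supports the condition.

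What is at stake is prespecification. If someone judges the assumptions unmet, the protocol tells them to set aside a sound analysis of the primary outcome and does not say what to do next. The replacement would then be chosen with outcome data in view, which opens the way to selective analysis. The same proviso covers every secondary outcome.

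**Working it through.** **1. The protocol's own sample size, to fix the arm size.** Inputs from Sample size planning: "a medium effect size of 0.53" and "Power was 0.8 and *p*<.05 with 10% attrition". Sidedness is not stated; two-sided is assumed.

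- Normal approximation: n per arm = 2(1.960 + 0.842)² / 0.53² = 2 × 7.849 / 0.2809 = 55.9, so 56.
- Two-sample t-test (noncentral t): 56.86, so 57 per arm and 114 in total.
- Attrition: 114 × 1.10 = 125.4, so 126; 114 / 0.90 = 126.7, so 127.

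The stated 126 is reproduced. The checks below use 57 evaluable women per arm.

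**2. Score range.** If the total is the sum of 12 items scored 1 to 9, it runs from 12 × 1 = 12 to 12 × 9 = 108. The score is bounded, so skewness is possible. The protocol gives no mean, SD or skewness for it, so the shapes below are assumptions.

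**3. Does robust GEE need the condition?** With complete data at two time points, the GEE group-by-time effect is the difference between arms in mean change, with robust standard error √(s₀²/n₀ + s₁²/n₁), where s² is the variance of the change scores in each arm. On a test data set this closed form and a fitted GEE gave the same p-value (0.2464). In 5,000 simulated null trials per scenario, the within-person correlation was 0.5 on the underlying normal scale. The condition was checked on post-intervention scores with Shapiro-Wilk in each arm and Levene, all at 5%:

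| Scenario | Type I error of robust GEE | At least one check fails |
|---|---|---|
| Normal, equal variances | 5.2% | 14.1% |
| Beta(4, 1.5) scaled to 12–108 (skewness about -0.7) | 4.9% | 96.3% |
| Same shape, intervention-arm spread cut to 0.6 of control | 5.9% | 99.9% |

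The Monte Carlo standard error at 5% is √(0.05 × 0.95 / 5000) = 0.3 percentage points. A separate robust GEE check gave 4.4% to 5.4%. In the third row the condition is false by construction, and GEE still comes close to its nominal level.

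**4. How far the failure rate depends on the rule.** The protocol names no rule, so several were tried at 57 per arm. The two skewed shapes are Beta(5, 2), skewness about -0.6, and Beta(4, 1.5), both with equal variances:

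| Rule for judging the assumptions | Failure rate, skewed scores |
|---|---|
| Skewness above 2 in absolute value, either arm | 0% |
| Skewness above 1 in absolute value, either arm | 9% to 19% across shapes and runs |
| Shapiro-Wilk and Levene on change scores | 17% to 19% |
| Shapiro-Wilk and Levene on raw post scores | 83% to 97% |

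With exactly normal data, the formal tests fail in 13% to 15% of trials. On raw scores they fail in 20% at skewness -0.2 and 44% at -0.4.

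**The case against.** Four points can be made for the protocol.

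*No formal pre-test is prescribed.* This is correct. A reader might infer that the primary method hinges on significance tests of normality and variance, and that a bounded score will probably fail them. The documents support neither inference: the text requires only that the assumptions be met, and gives nothing on the shape of the score. The high failure rates come from one assumed rule on assumed shapes.

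*How assumptions are checked, and what follows, usually belongs in the SAP.* This also stands in part. The SAP is not at hand, so one cannot say that the trial has no primary analysis if the condition fails, only that the protocol names none. But the condition itself is in the protocol. An SAP that follows it inherits the error; an SAP that drops it departs from the protocol.

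*The protocol does not say which standard errors it means.* Model-based GEE standard errors do lean on the working variance, so a concern about equal variances would have some basis there. Robust standard errors remove it, and normality is not required in either case.

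*No harm to inference has been shown.* This is true. No error rate was estimated for a check-then-switch procedure, and in the skewed scenarios the ordinary t-test also held its level (5.0% and 5.2%). The t-test is not offered as a fallback, though, and in its classical form it assumes the same two things. Its lack of an explicit proviso adds little, because the closing qualifier in that sentence could be read as covering it.

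**Conclusion.** The point holds as a wrongly stated condition. The protocol makes its primary analysis depend on two properties that GEE with robust standard errors does not require, and names no alternative if they are judged absent. The consequence is avoidable freedom to choose the primary analysis after outcome data are seen. Bias or an inflated error rate has not been demonstrated.

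How often the condition would be judged unmet is unknown. With equal variances in the two arms, the illustrative range is about 0% to 97%, depending almost entirely on the rule and the score shape assumed. Robust GEE keeps type I error at about 4% to 6% in every scenario tried. These figures assume 57 evaluable participants per arm, complete data, a two-sided 5% level, the stated Beta shapes and, for GEE and the change scores, a within-person correlation of 0.5. The conclusion does not depend on the simulations, because it follows from what GEE requires and from the wording of the sentence.

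**What to change.** Delete the proviso from the main RCT's Data analysis section. State in its place: *The primary outcome will be analysed by GEE with robust standard errors, regardless of the results of any check of normality or variance. Any analysis prompted by the distribution of the outcome will be a sensitivity analysis only.* The same sentence can cover the secondary outcomes.

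The link function, the working correlation and the type of sensitivity analysis can be left to the SAP. The cost is one sentence, to be changed before outcome data are seen. The sample size of 126, the visits and the data collected stay as they are.
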